### Proposed sample size

Cluster randomisation will be used, randomising at the school level, because the intervention will involve whole schools and participating classes. Based on results from our previous work on schools in a national sample, we estimate the standard deviation for the amount of vegetables eaten to be 85 g and for fruit 143 g. The associated intraclass correlation coefficient for total vegetables from Project Tomato was 12.5% and for fruit 11.4% (unpublished results). This sample of 50 children (one year 3 class and one year 4 class) from each school, will give a design effect of approximately 6.6 for vegetables and 7.1 for fruit to take account of the cluster randomisation. To have 90% power to detect a 0.5 portion difference in vegetable intake, 627 per group are required, i.e. about 13 schools using 2 classes from each school. To have 90% power to detect a 1 portion difference in fruit intake, 482 per group are required, i.e. about 10 schools. Based on results from our evaluation of the School Fruit and Vegetable Scheme, 75% who completed the Child And Diet Evaluation Tool (CADET) at baseline also completed the final follow up CADET. To allow for this margin of safety, 16 schools per group will be selected in each group apart from the intensive intervention group where it is only possible for 10 schools to be involved. The size of effect the study is powered to detect, (one half of a portion of vegetables or one portion of fruit) was chosen because it was considered the smallest improvement in intake that was worthwhile detecting with the achievable sample size, and considering the nature of the intervention.

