### School withdrawal

If a school wishes to withdraw from the trial, the study team will post a data collection form to the head/class teacher along with a freepost envelope. The data collection form will record the following: reasons for withdrawal; whether anything could have been done to make taking part in the study easier; if they no longer want to take part in the intervention and receive information/training/materials and if they still allow us to use data collected to date and to collect data at round two i.e. follow-up collection in October 2011.

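### The allowance for 25% loss does not reconcile with the vegetable sample size (600 completers against 627), and Trial 1, capped at 10 intensive schools, falls short of the stated 90% power

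*Protocol article*

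**What the plan says.** All the inputs are in the Protocol article under Proposed sample size. For variability, "we estimate the standard deviation for the amount of vegetables eaten to be 85 g and for fruit 143 g". For clustering, the "intraclass correlation coefficient for total vegetables from Project Tomato was 12.5% and for fruit 11.4" per cent. The cluster is set by "This sample of 50 children (one year 3 class and one year 4 class) from each school", which is said to give a "design effect of approximately 6.6 for vegetables and 7.1 for fruit". The vegetable target follows: "To have 90% power to detect a 0.5 portion difference in vegetable intake, 627 per group are required, i.e. about 13 schools". For fruit, 482 per group, about 10 schools, are required for a difference of one portion.

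The section then reports that, in an earlier evaluation, 75% of the children who completed the dietary tool at baseline also completed it at final follow-up. It concludes: "To allow for this margin of safety, 16 schools per group will be selected". The intensive arm is the exception, because only 10 schools can be taken. The section closes by describing the study as a whole as powered for half a portion of vegetables or one portion of fruit.

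Trial 1 is therefore 10 against 16 schools and Trial 2 is 16 against 16. A separate section, School withdrawal, sets out what happens "If a school wishes to withdraw from the trial".

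**The concern.** The step from 13 to 16 schools is offered as the allowance for a 25% loss, but dividing the requirement by 0.75 does not give 16. Vegetables set the sample size, so a reader who relies on the 90% needs to know whether it survives the loss that the plan itself expects.

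Two things make this hard to judge from the text. The 627 rests on a design effect for 50 children per school, while the expected loss would change the number per school, the number of schools, or both, and the section does not say which. And the 90% figure assumes two groups of about 13 schools, which one arm of Trial 1 cannot reach even before any loss. No power is given for that comparison.

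**Working it through.** **Assumptions not in the document.** A portion is taken as 80 g, so half a portion is 40 g, and the test as two-sided at 5%. The section states neither, but together they reproduce both published sample sizes.

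**1. Reproducing the plan's figures.**
- Vegetables: n = 2 × (1.96 + 1.2816)² × 85² / 40² = 94.9, rounded up to 95. 95 × 6.6 = 627, as stated. 627/50 = 12.5, about 13 schools.
- Fruit: 2 × (1.96 + 1.2816)² × 143² / 80² = 67.15, rounded up to 68. 68 × 7.1 = 482.8, against 482 stated.

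**2. The attrition step on the plan's own count.**
- Vegetables: 627/0.75 = 836 children; 836/50 = 16.7, so 17 schools. From the rounded 13 schools, 13/0.75 = 17.3.
- Sixteen schools: 16 × 50 = 800 at baseline; 800 × 0.75 = 600 at follow-up, 27 short of 627. On this count 16 schools cover a loss of 1 − 627/800 = 21.6%, not 25%.
- Fruit: 482/0.75 = 643 children, or 12.9 schools, so 16 are enough.

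**3. Power when the design effect follows the retained cluster size.** With m completers per school and the stated vegetable ICC of 0.125, the design effect is 1 + (m − 1) × 0.125. At m = 50 this is 7.125. The 6.6 printed for vegetables is what the fruit ICC gives (1 + 49 × 0.114 = 6.586). That mismatch is a separate matter; here the stated vegetable ICC is used throughout.

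If all the loss is children within retained schools, m = 37.5, the design effect is 1 + 36.5 × 0.125 = 5.5625, and the need is 95 × 5.5625 = 528 completers, fewer than the 600 expected.

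Effective n per group = schools × m / design effect; SE = 85 × √(1/n₁ + 1/n₂); power = Φ(40/SE − 1.96). The last column replaces the normal with a noncentral t on (schools − 2) degrees of freedom. The Trial 2 rows after the first hold completers at 600 per group.

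| Schools | m | Design effect | Effective n | SE (g) | Normal | t |
|---|---|---|---|---|---|---|
| Trial 2, 16 v 16, no loss | 50 | 7.125 | 112.3 | 11.34 | 94.1% | 92.7% |
| 16 v 16, children only lost | 37.5 | 5.5625 | 107.9 | 11.57 | 93.3% | 91.7% |
| 15 v 15 | 40 | 5.875 | 102.1 | 11.90 | 92.0% | 90.1% |
| 14 v 14 | 42.9 | 6.232 | 96.3 | 12.25 | 90.4% | 88.2% |
| 13 v 13 | 46.2 | 6.644 | 90.3 | 12.65 | 88.5% | 85.9% |
| 12 v 12, schools only lost (extreme) | 50 | 7.125 | 84.2 | 13.10 | 86.3% | 83.1% |
| Trial 1, 10 v 16, no loss | 50 | 7.125 | 70.2, 112.3 | 12.93 | 87.1% | 84.3% |
| Trial 1, 10 v 16, children only lost | 37.5 | 5.5625 | 67.4, 107.9 | 13.20 | 85.8% | 82.8% |

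If whole schools go on top of a 25% loss of children, 15 v 15 at 37.5 per school gives 91.7% (t: 89.8%) and 14 v 14 gives 89.9% (t: 87.5%).

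**4. Sensitivity to the ICC.** With 0.114, the value that matches the printed 6.6, Trial 2 gives 94.8% if only children are lost and 88.8% at 12 v 12. Trial 1 gives 89.6% with no loss and 88.2% with child loss (t: 87.0% and 85.5%), still under 90%.

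**The case against.** The strongest reply is that 600 against 627 compares unlike quantities. The 627 belongs to 50 completers per school; 600 completers in 16 schools are 37.5 per school, where about 528 are enough. The only attrition figure in the document is a completion rate among children, so loss within schools is a natural reading, and on it Trial 2 exceeds 90% under either method. The text also speaks loosely of a safety margin and never states that 627 completers will remain. All of this stands, and it limits the point. It does not reconcile the step as printed: the section computes the design effect at 50, never recomputes it, and does not say how the loss falls.

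A reader might go further and infer that 90% power holds only if no whole school is lost. The figures do not support that: with total loss held at 25%, one school per group can go with power still at 90% or more under either method, and two on the normal approximation. Nor does the School withdrawal section forecast such losses. It is a procedure without a rate, and its form asks whether follow-up data may still be collected, so a school that withdraws is not necessarily lost to the outcome. The 12 v 12 case, with four of 16 schools gone in each group, is an extreme and not an expectation.

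On Trial 1, it can fairly be said that the cap of 10 is disclosed and that attrition costs only about one percentage point (87.1% to 85.8%). The shortfall there comes from the cap. What remains is that the power for that comparison is not given, while the section describes the study without distinction as powered for half a portion of vegetables.

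**Conclusion.** The point holds in a limited form. The printed allowance does not reconcile for vegetables: simple division asks for 17 schools per group, and 16 leave 600 completers against 627. Fruit is not affected.

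It would be wrong to infer from the missing 27 children that Trial 2 is underpowered. Its vegetable power is about 93% (t: 92%) if the loss is mainly within schools, at or near 90% with one or two whole schools lost per group, and about 86–89% (t: 83–86%) only if most of the 25% is whole schools.

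Trial 1 does not have the stated 90% for half a portion of vegetables, even with no loss: about 87%, or 86% with 25% child loss (t: 84% and 83%). It stays below 90% at either stated ICC.

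These figures rest on the 80 g portion and two-sided 5% level inferred above, the stated SD of 85 g, 50 children per school at baseline, and equal loss across schools within each scenario.

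**What to change.** Rewrite the attrition step under Proposed sample size:
- give the 600 completers expected in each 16-school group, and do not leave 16 schools to be read as 627 inflated for 25% loss;
- give the design effect at the retained cluster size (5.56 at 37.5 per school, so about 528 needed);
- state the assumed pattern of loss between children and whole schools;
- report vegetable power separately: Trial 2 about 92–93% under child-level loss, with 83–86% as the extreme in which all loss is whole schools; Trial 1 about 83–86% under child-level loss;
- confine the general statement that the study is powered for half a portion of vegetables to the comparison for which it holds;
- state the portion weight and significance level used.

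This changes text only and needs no extra schools. The cost is that the power stated for Trial 1 becomes slightly less favourable.

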### Discontinuation criteria

Analysis will follow the principle of intention-to-treat as far as possible. We will therefore include in analyses all schools and children initially randomised, including them for analysis purposes in the intervention group originally allocated to them. To this end, all reasonable and ethical steps will be taken to ensure completeness of follow-up of outcome measures.

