## Methodology

### Sampling and recruitment of schools

#### Trial 1 – intensive vs. Less intensive intervention

The RHS plan to establish their Campaign for School Gardening to schools in the London region in the autumn of 2009. The RHS Campaign provides intensive support in each region to 10 schools through support from an RHS School Gardening Regional Advisor (the intensive intervention). The remaining schools will have access to support through twilight training sessions for staff and other activities (the less intensive intervention).

Twenty-six schools will be recruited from four boroughs in London: Wandsworth; Tower Hamlets; Greenwich; and Sutton. Of the 26 schools we will randomly allocate 10 schools to receive the intensive intervention and 16 schools to receive the less intensive intervention. The allocation sequence will be generated by the trial statistician. All schools will be allocated at the same time. Time between notification of allocation and the start of the intervention will be as short as possible. It will not be possible to randomise schools to receive no intervention at all since the RHS is committed to providing support to all schools who register an interest in the Campaign. As a consequence of this, we will recruit a second set of schools into a linked trial.

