### Proposed outcome measures

#### The primary outcome measure will be the following

· Food:

· Daily portions of fruit and vegetable intake at follow-up (15 months after baseline)

· Daily portions of fruit intake

· Daily portions of vegetable intake

The effectiveness of either intervention would be determined by an increase in mean intake in one of the following: mean intake of fruit, mean intake of vegetables, or mean intake of fruit and vegetables at follow-up after adjusting for baseline

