### Primary analyses

A random or fixed intercepts model of primary and secondary outcomes will be used allowing for hierarchical structure of data caused by cluster randomisation: child within class within school. MLwiN [47] will be used for this analysis. The single covariate for the intervention group will be included in the model (treated as a random effect since schools in the trial are themselves a random sample from the population of schools).

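### The primary analysis is said to include all randomised children, but the primary model as written uses only those with a follow-up CADET and omits the stated baseline adjustment

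*Protocol article*

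**What the plan says.** All places are in the protocol article.

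- **Discontinuation criteria.** The section opens with "Analysis will follow the principle of intention-to-treat as far as possible". The next sentence carries no qualifier: "We will therefore include in analyses all schools and children initially randomised, including them for analysis purposes in the intervention group originally allocated to them". The only means named is effort at follow-up: "all reasonable and ethical steps will be taken to ensure completeness of follow-up of outcome measures".
- **Proposed sample size.** Retention is taken from an evaluation of the School Fruit and Vegetable Scheme, in which "75% who completed the Child And Diet Evaluation Tool (CADET) at baseline also completed the final follow up CADET". It is used to choose the number of schools: "To allow for this margin of safety, 16 schools per group will be selected in each group apart from the intensive intervention group".
- **Proposed outcome measures.** The first primary outcome is "Daily portions of fruit and vegetable intake at follow-up (15 months after baseline"). This section and the Research questions section both say that effectiveness is judged on follow-up intake adjusted for baseline.
- **Primary analyses.** The model is multilevel, with children nested in classes and classes in schools, and "The single covariate for the intervention group will be included in the model". Baseline intake is not mentioned.
- **Child withdrawal and Ethical considerations.** Withdrawn children get no further questionnaire, and the intake of opted-out children is not recorded.
- **School withdrawal and the food diary section.** Withdrawing schools are asked whether follow-up data may still be collected. A home diary that is not returned is replaced by recall.

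**The concern.** The stated population and the stated model do not match. A model whose response is follow-up intake, with arm as its only explanatory variable, takes no information from a child whose follow-up intake is missing. The protocol plans for a sizeable share of such children, and by design has some with no intake data after withdrawal or none at all. The unqualified sentence about including everyone therefore cannot be met by the analysis described.

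Two things are at stake. The first is description: the Subgroup analyses section sets the intention-to-treat result beside an efficacy subset, so the reader must know which children the intention-to-treat result rests on. The second is bias. Schools are not blinded and contact with the regional advisor differs by arm, so completion could differ by arm too, although nothing in the protocol shows that it will. With no baseline term in the model, a link between baseline intake and completion that differs by arm passes into the estimated effect.

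**Working it through.** **1. The plan's own figure.** Inputs from Proposed sample size: SD 85 g for vegetables, 90% power, half a portion, design effect 6.6. Assumed: an 80 g portion (target 40 g) and two-sided 5%.

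n = 2 × (1.96 + 1.2816)² × 85² / 40² = 94.9, rounded up to 95. Then 95 × 6.6 = 627, the stated number per group. The 40 g target is therefore a fair reading.

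**2. Children who can enter the model.** Inputs: 50 children per school; in Trial 1 "we will randomly allocate 10 schools to receive the intensive intervention and 16 schools to receive the less intensive intervention"; in Trial 2, 16 schools in each arm; retention 75%.

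| | Children | With follow-up (× 0.75) | Without |
|---|---|---|---|
| Trial 1 (26 schools) | 26 × 50 = 1,300 | 975 | 325 |
| Trial 2 (32 schools) | 32 × 50 = 1,600 | 1,200 | 400 |

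These counts treat all 50 children per school as baseline completers.

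**3. Power.** SE = 85 × √[DE × (1/n₁ + 1/n₂)], with DE = 1 + (m − 1) × 0.125, m the number of children analysed per school, and power = Φ(40/SE − 1.96).

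- Trial 2, m = 50: DE = 7.125, SE = 85 × √(7.125 × 2/800) = 11.3 g, power 94.1%.
- Trial 2, m = 37.5: DE = 5.5625, SE = 85 × √(5.5625 × 2/600) = 11.6 g, power 93.3%.
- Trial 1, same formula with 10 and 16 schools: 87.1% falls to 85.8%.

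If losses are spread evenly over schools, precision is hardly affected.

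**4. Possible bias in the arm-only model.** Every input in this step that is not an SD, an ICC or a school count is assumed. Trial 2 vegetables, no true effect. In one arm 80% complete, regardless of intake. In the other 70% complete, with log-odds of completion rising by s = 0.4 to 0.7 per SD of baseline intake (odds ratio e^0.4 = 1.5 to e^0.7 = 2.0). The correlation r between baseline and follow-up intake is 0.2 to 0.5, at both child and school level.

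Among completers in the second arm, mean standardised baseline intake is c = ∫ z · expit(a + sz) · φ(z) dz / 0.70, with a set to give 70% completion. This gives c = 0.116 for s = 0.4 (a = 0.88) and c = 0.192 for s = 0.7 (a = 0.94). The within-school share of the variance is 1 − 0.125 = 0.875. The shift in the follow-up comparison is about r × 0.875 × c × 85:

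- Smallest: 0.2 × 0.875 × 0.116 × 85 = 1.7 g.
- Largest: 0.5 × 0.875 × 0.192 × 85 = 7.1 g.

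Simulation under the same assumptions gave 1.6 to 7.3 g with a standard error of about 11.5 g. So the range is about 2 to 7 g: 2/40 = 5% to 7/40 = 18% of the target, and 2/11.5 = 0.2 to 7/11.5 = 0.6 of a standard error. With s = 0 the bias is zero. With baseline intake in the model the simulated bias is about zero.

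**5. Departure from missing at random.** If the 25% without follow-up in one arm differ from what the model assumes by d SD, the estimate moves by 0.25 × d × 85: 2.1, 4.3 and 6.4 g for d = 0.1, 0.2 and 0.3.

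**The case against.** The strongest reply is that this is a condensed article, and that the handling of missing outcomes normally sits in an analysis plan, which is not shown. That is right as far as it goes: the absence of an imputation method is no fault here, and a fuller plan may contain one. What stands is narrower. The article does state a population and a model, and the two do not agree.

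A second reply is that the paragraph begins with a qualifier and mainly promises analysis by allocated arm. This is fair, and the model does not contradict that promise. But the sentence on who is included has no qualifier, and the reader is not told whether the qualifier means completers, imputation or a joint model.

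A third reply is that the bias disappears under the baseline adjustment that the article states elsewhere. This is also correct. The simulated bias belongs to the model in Primary analyses, which omits that adjustment, and the size of the problem depends on which section is followed.

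Four stronger readings are tempting and are not supported:

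- That the analysis is per-protocol. It is not: children with follow-up data are analysed as allocated, whatever their adherence.
- That the trial expects to lose a quarter of all randomised children. The 75% comes from another evaluation, refers to baseline completers, and serves as a planning margin.
- That school withdrawal ends follow-up. The School withdrawal section asks those schools to allow follow-up collection, and recall covers home diaries that are not returned.
- That the trial's result will be biased. The completion patterns in step 4 appear nowhere in the protocol.

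**Conclusion.** The point holds in a limited form. The sentence that all randomised children are included is broader than the model in Primary analyses can deliver, and that model also drops the baseline adjustment stated in two other sections. If the planning figure applies, about three quarters of the children contribute. The cost in power is about one percentage point. The cost in bias ranges from zero, if completion is unrelated to intake, to about 2 to 7 g of vegetables under the illustrative assumptions, and is about zero after baseline adjustment if completion depends only on baseline intake and arm. The mismatch follows from the text. The bias figures show what could happen and rest on inputs that the documents do not give. The change is worth making because it is cheap and settles both inconsistencies together.

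**What to change.** - **Primary analyses.** Fit baseline and follow-up intake as a two-occasion response in MLwiN, with occasion within child, child within class and class within school, and the arm effect at follow-up only. This adjusts for baseline, and every child with at least one CADET contributes under a missing-at-random assumption, which should be stated.
- **Sensitivity analysis.** Add one analysis that shifts the assumed mean of children without follow-up by arm, for example by 0.1 to 0.3 SD in one arm. For vegetables this moves the estimate by about 2 to 6 g.
- **Discontinuation criteria.** Replace the unqualified sentence with a definition of the analysed set: children by allocated arm with at least one CADET. State that children with none, such as those opted out, are outside it. The joint model does not bring them in.
- **If the joint model is not adopted.** Describe the primary analysis as children with follow-up data, by allocated arm, adjusted for baseline, and add baseline intake to the model.

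No extra data or software are needed. The cost is new wording in two sections, one further analysis and a slightly more complex model.

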### School withdrawal

If a school wishes to withdraw from the trial, the study team will post a data collection form to the head/class teacher along with a freepost envelope. The data collection form will record the following: reasons for withdrawal; whether anything could have been done to make taking part in the study easier; if they no longer want to take part in the intervention and receive information/training/materials and if they still allow us to use data collected to date and to collect data at round two i.e. follow-up collection in October 2011.

### Child withdrawal

A parent may request that an individual child is no longer part of the trial. This request may go either to the school, the RHS or the study team at the University of Leeds. Whoever is the first point of contact with the parent must inform the other relevant groups (school/RHS/University of Leeds) by telephone or letter; this will be recorded in the database. On receipt of this information the study team will send a letter to inform the class teacher that the child is to be withdrawn from the study. A data collection form and freepost envelope will be sent via the class teacher to the parent. A covering letter will make clear to the parent that while the child will not receive any questionnaire for completion, the child will not be left out of whole class activities as to do so would involve taking the child out of the class whilst these activities were occurring.

